#### Handling of study withdrawals

No subjects who withdraw from the study for any reason will be replaced, which is fully consistent with the ITT principle. All randomized subjects, regardless of whether they complete the study or not, will be included in the primary ITT analysis. The sample size calculation for this trial has already accounted for a conservative 20% dropout rate, so the statistical power of the study will be maintained even with the expected number of withdrawals.

For subjects who withdraw before completing all primary outcome assessments, de-identified data collected before withdrawal will be retained for statistical analysis. No additional follow-up data will be collected without the subject’s explicit written consent.

#### Blinding procedures

This is a patient- and outcome assessor-blinded randomized controlled trial. The following study personnel remain fully blinded to the group allocation throughout the entire study period:

All study participantsThe independent outcome assessor ([name], responsible for pain score assessment, diaphragmatic function measurement, and pulmonary function testing)The intraoperative general anesthesia management teamAll post-anesthesia care unit (PACU) and ward nursing staffThe data management teamThe independent statistician

Only two study personnel are aware of the group allocation: [name], the dedicated anesthesiology nurse responsible for study drug preparation and envelope management, and [name], the anesthesiologist exclusively performing the ultrasound-guided nerve block procedure. Strict measures have been implemented to minimize potential bias introduced by these unblinded personnel:

Complete separation of roles: [name] does not participate in any baseline or postoperative outcome assessments, patient recruitment, or data analysisProhibition of any communication regarding group allocation between unblinded personnel and all blinded study staffStandardized preparation of study drugs in identical 5 mL syringes with no distinguishing marksApplication of an opaque sterile dressing to the puncture site after the block procedure to maintain patient blinding

### Baseline pulmonary function test and diaphragmatic excursion measurement

Subjects sign the written informed consent form one day before surgery, and remain fully blinded to their group allocation throughout the perioperative period. No premedication is administered to any subject in the ward before surgery.

On the day of elective surgery, all subjects follow the standard preoperative fasting protocol, with 8 h of fasting for solid food and 2 h of fasting for clear liquids. After entering the operating room, a peripheral venous access is established on the non-operative upper limb of each subject, followed by a rapid infusion of 8 mL/kg lactated Ringer’s solution over 15–20 min for initial volume expansion. For patients with a history of cardiovascular disease (including heart failure, coronary artery disease, or hypertension), the infusion rate and total volume will be individually adjusted based on clinical assessment to avoid volume overload. Standard non-invasive monitoring is initiated immediately, including continuous electrocardiogram (ECG), non-invasive blood pressure (NIBP), and pulse oxygen saturation (SpO₂). Baseline vital signs (heart rate, systolic blood pressure, diastolic blood pressure, mean arterial pressure, and SpO₂) are recorded before any anesthetic or study intervention, and all intraoperative vital signs are continuously documented in the electronic anesthesia record system throughout the procedure.

Immediately after the above preoperative preparation is completed and strictly before the implementation of the study intervention (ultrasound-guided subparaneural block at the brachial plexus upper trunk bifurcation), all baseline diaphragmatic excursion and pulmonary function measurements are performed. The core purpose of these measurements is to obtain paired baseline data for the primary and secondary endpoints of this patient- and outcome assessor-blinded randomized controlled trial, so as to evaluate the differences in diaphragmatic function and pulmonary function between the 2 mL and 5 mL 0.375% ropivacaine groups after the study intervention.

All baseline and postoperative pulmonary function testing and diaphragmatic excursion measurements are independently completed in full by [name]. Prior to trial initiation, [name] has completed standardized, centralized training for ultrasound diaphragmatic function assessment and pulmonary function testing, with a verified track record of more than 200 standardized, qualified procedures, to ensure the standardization of operational processes, the repeatability of measurements, and the reliability of the collected data, and to minimize inter-observer and intra-observer variability. To strictly maintain the integrity of the patient- and outcome assessor-blinded design, [name] remains fully blinded to the group allocation of all subjects throughout the entire study period.

The entire study intervention procedure is independently completed in full by [name], a senior anesthesiologist with extensive experience in ultrasound-guided brachial plexus block. To strictly enforce the separation of roles and avoid unblinding, [name] is prohibited from participating in any baseline measurement procedures, has no access to the baseline measurement data collected by [name], and does not participate in postoperative outcome assessment or data statistical analysis. [name] only obtains the pre-prepared study drug corresponding to the subject’s enrollment number from [name], the dedicated anesthesiology nurse responsible for randomization management and study drug preparation, only after [name] has fully completed all baseline measurements, archived the original data, and handed over the subject to the surgical team. [name] is only aware of the injection volume of the study drug for the individual enrolled subject, and is strictly prohibited from disclosing any allocation-related information to [name], the subject, the anesthesia management team, or the surgical team.

All measurements are performed with the subject placed in a unified, standardized semi-sitting position, with the head of the bed elevated at 30 degrees, the head maintained in a neutral position, and both upper limbs placed naturally on both sides of the body. This body position is strictly consistent between the baseline measurement and the postoperative follow-up assessment, to avoid deviations in diaphragmatic excursion and pulmonary function test results caused by postural differences, and ensure the comparability of paired pre- and post-intervention data.

For diaphragmatic excursion measurement, the anterior subcostal approach is adopted by [name], with the liver (for subjects undergoing right-sided shoulder surgery) or the spleen (for subjects undergoing left-sided shoulder surgery) used as the acoustic window. The measurement is performed using the SONOSITE SII® ultrasound system (FUJIFILM SonoSite, Inc., Bothell, USA) equipped with a low-frequency (1 to 5 MHz) convex array probe. After clearly visualizing the continuous diaphragmatic pleural line, the probe position and angle are fixed, and the system is switched to M-mode to record the waveform of diaphragmatic movement during deep breathing. Three stable and reproducible diaphragmatic movement waveforms during deep breathing are continuously recorded for each subject, the excursion amplitude (cm) of the ipsilateral hemidiaphragm is measured for each valid waveform, and the average value of the three measurements is calculated and documented as the baseline diaphragmatic excursion value of the subject. All original ultrasound images of the measurements are archived in real time for subsequent review and data verification.

For pulmonary function testing, [name] uses a CONTEC SP80B handheld spirometer (CONTEC Medical Systems Co., Ltd., Hebei, China) with the subject remaining in the same standardized semi-sitting position. The subject wears a nose clip and holds a disposable mouthpiece, and completes forced expiration maneuvers following standardized verbal instructions, in strict accordance with international pulmonary function testing guidelines. Three valid and reproducible forced expiration measurements are completed for each subject, with invalid curves (such as those caused by insufficient expiratory time, poor initial expiratory burst, or air leakage) excluded. The forced expiratory volume in 1 s (FEV1) and forced vital capacity (FVC) of each valid measurement are recorded, and the average value of the three valid measurements is calculated and documented as the baseline FEV1 and FVC values of the subject. The baseline FEV1/FVC ratio is calculated simultaneously, and subjects with a baseline FEV1/FVC < 70% are excluded from the trial in accordance with the pre-specified exclusion criteria.

All baseline measurement data are entered into a standardized case report form (CRF) marked only with the subject’s unique study ID (no group allocation information) in real time by [name], and then independently double-entered into the study-specific locked electronic database by two other researchers who are not involved in the measurement or intervention procedures, with cross-verification performed to ensure the integrity, accuracy and traceability of the data. Throughout the study, no communication related to the subject’s group allocation, intervention details, or baseline measurement results is allowed between [name] and [name], to strictly maintain the blind design and eliminate any potential assessment bias.

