#### Postoperative pulmonary function test and diaphragmatic excursion measurement

All postoperative pulmonary function and diaphragmatic excursion measurements are independently completed by [name], the same investigator who performed the preoperative baseline assessments, to eliminate inter-operator variability and ensure the consistency and comparability of paired pre- and post-intervention data.

The measurements are performed when the subject is fully awake, has stable spontaneous breathing, and can accurately follow standardized verbal instructions, strictly before discharge from the PACU. The subject’s body position, equipment used, operational procedures, quality control standards, and data calculation methods for the measurements are completely consistent with those used for the preoperative baseline assessments.

Hemidiaphragmatic paralysis (HDP) is defined as a decrease in postoperative diaphragmatic excursion of ≥75% compared with the baseline value, or the presence of paradoxical diaphragmatic movement during breathing. The incidence of HDP is recorded as one of the co-primary endpoints of the trial. The absolute and percentage changes in diaphragmatic excursion, forced expiratory volume in 1 s (FEV1), and forced vital capacity (FVC) from baseline to postoperative measurement are calculated for each subject as key secondary endpoints of the trial.

All postoperative measurement data are entered into a standardized CRF marked only with the subject’s unique study ID in real time, and independently double-entered into the study-specific locked electronic database by two other researchers not involved in the measurement or intervention procedures, with cross-verification performed to ensure the integrity, accuracy and traceability of the paired data.

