### Data collection

All study data are collected at pre-specified time points in accordance with the study protocol, with the specific collection content as follows:

*Screening and baseline data*: Subject demographic information (age, gender, height, weight, BMI), ASA physical status classification, preoperative comorbidities (hypertension, diabetes, cardiovascular disease, chronic pulmonary disease, etc.), past medical history (ipsilateral shoulder or cervical surgery history, chronic pain history, allergy history), preoperative vital signs (heart rate, blood pressure, SpO₂), preoperative laboratory test results (hemoglobin, platelet count, coagulation function, liver and kidney function), and preoperative pulmonary function and diaphragmatic excursion baseline measurements (FEV1, FVC, FEV1/FVC ratio, ipsilateral diaphragmatic excursion value).*Intraoperative data*: general anesthesia related data (induction and maintenance drug dosage, anesthesia duration, surgery duration, laryngeal mask airway extubation time, emergence time), intraoperative hemodynamic parameters, total dosage of intraoperative analgesic and vasoactive drugs, intraoperative fluid balance (infusion volume, blood loss, urine output), and any protocol deviations or adverse events during the operation.*Post-anesthesia care unit (PACU) data*: Pre-rescue analgesia NRS pain score assessed immediately after the patient regains full consciousness from general anesthesia (before rescue analgesia in PACU), postoperative diaphragmatic excursion and pulmonary function measurements, PACU stay duration, rescue analgesia administration details, emergence and recovery related indicators, and any adverse events during the PACU stay.*Safety and compliance data*: Detailed records of all perioperative adverse events and serious adverse events, including onset time, severity, causal relationship with the study intervention, treatment measures, and final outcome; detailed records of subject withdrawal, loss to follow-up, and protocol deviations, including specific reasons and corresponding handling measures.

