### Outcomes

#### Primary outcomes

This trial adopts a dual co-primary endpoint design to simultaneously verify the non-inferiority of analgesic efficacy and the superiority of diaphragmatic safety of the 2 mL local anesthetic regimen:

1 Pre-rescue analgesia NRS pain score assessed immediately after the patient regains full consciousness in the PACU

*Evaluation tool*: 11-point NRS (0 = no pain, 10 = the worst imaginable pain)*Evaluation time*: Immediately after full consciousness and ability to accurately report discomfort, strictly before any rescue analgesia administration*Study objective*: To test the non-inferiority of 2 mL 0.375% ropivacaine compared with 5 mL 0.375% ropivacaine in postoperative analgesic efficacy, with a predefined non-inferiority margin of 1 point on the NRS scale.

2 Incidence of ipsilateral hemidiaphragmatic paralysis (HDP) assessed before discharge from the PACU

*Definition*: Complete paresis: A reduction in diaphragmatic movement of more than 75%, no movement, or paradoxical movement. Partial paresis: A reduction in diaphragmatic movement between 25 and 75%.*Evaluation tool*: Ultrasound measurement of diaphragmatic excursion via the anterior subcostal approach (M-mode)*Evaluation time*: Strictly before discharge from the PACU, performed by the same blinded investigator who conducted the baseline measurements*Study objective*: To test the superiority of 2 mL 0.375% ropivacaine compared with 5 mL 0.375% ropivacaine in reducing the risk of HDP.

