##### Handling of missing data

For primary outcome data missing due to subject withdrawal or loss to follow-up, multiple imputation (MI) will be performed using 5 independent imputation cycles. Predictors for imputation will include baseline demographic and clinical characteristics (age, gender, BMI, ASA physical status), intraoperative factors (surgery duration, anesthesia duration, total sufentanil dosage), and available partial outcome data. A fixed random seed (12345) will be set to ensure reproducibility of the imputation results.For secondary outcome data with missing values, complete-case analysis will be performed, and the proportion of missing data will be reported.No imputation will be performed for safety data; all reported adverse events will be included in the safety analysis regardless of subject withdrawal status.

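### No preoperative pain score is among the listed baseline data or imputation predictors, so the NRS co-primary cannot be adjusted for, or imputed from, the patient's own earlier pain: a modest, cheap gain forgone

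*Protocol article*

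**What the plan says.** **Baseline session.** The section on baseline pulmonary function and diaphragmatic excursion states that, before the block, "all baseline diaphragmatic excursion and pulmonary function measurements are performed". It gives the reason: "The core purpose of these measurements is to obtain paired baseline data for the primary and secondary endpoints". The same sentence then limits that purpose: "so as to evaluate the differences in diaphragmatic function and pulmonary function between the 2 mL and 5 mL 0.375% ropivacaine groups".

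**Co-primaries.** HDP is judged against the patient's own baseline. The postoperative measurement section defines it as "a decrease in postoperative diaphragmatic excursion of ≥75% compared with the baseline value", or paradoxical movement. The pain co-primary is a single postoperative value: "Pre-rescue analgesia NRS pain score assessed immediately after the patient regains full consciousness in the PACU".

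**Data listed.** The Data collection section opens with "All study data are collected at pre-specified time points in accordance with the study protocol, with the specific collection content as follows". Its baseline items cover demographics, ASA class, comorbidities, medical history, vital signs, laboratory tests and "preoperative pulmonary function and diaphragmatic excursion baseline measurements (FEV1, FVC, FEV1/FVC ratio, ipsilateral diaphragmatic excursion value"). The only pain item is a history of chronic pain, which is not a score.

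**Analysis.** The section on primary outcomes compares mean NRS by an equal-variance two-sample t-test with no covariate, against a margin of 1 point. Missing primary outcomes are multiply imputed: "Predictors for imputation will include baseline demographic and clinical characteristics (age, gender, BMI, ASA physical status"), together with surgery and anesthesia duration, sufentanil dose and any partial outcome data. Preoperative pain is not named.

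**The concern.** The Introduction describes the target conditions as leading causes of chronic shoulder pain, and the PACU score asks about discomfort in the arm or shoulder, the region that brought the patient to surgery. The eligibility criteria exclude chronic pain only when it has needed regular opioids for more than 3 months, so preoperative pain may still vary widely among those enrolled. If it carries through to the PACU score, an earlier score on the same scale is a natural covariate and a natural imputation predictor.

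Three things are at stake, none of them the validity of the trial:
- the width of the confidence interval whose upper bound is compared with 1 point;
- the ability to see whether one arm happened to start with more pain, and to adjust for it;
- the quality of imputation for missing NRS scores, in a plan that allows for 20% dropout.

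A later SAP can choose an adjusted analysis, but it cannot adjust for a score that nobody recorded.

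**Working it through.** **1. The plan's own figure.** Inputs from the sample size section: margin δ = 1, SD σ = 1.6, one-sided α = 0.025, power 0.80, true difference 0.

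n = 2(1.96 + 0.84)² × 1.6² / 1² = 2 × 7.84 × 2.56 = 40.14 per group.

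The stated 40 reproduces (41 if rounded up), and 40 / (1 − 0.20) = 50 per group. The calculation uses the unadjusted SD, so it does not depend on a baseline pain score.

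**2. What a baseline score would add.** Let r be the correlation between preoperative and PACU NRS. The document gives no r, so a range is assumed. With the score as an ANCOVA covariate:
- residual SD = 1.6 × √(1 − r²);
- SE of the difference = residual SD × √(2/n);
- power from the noncentral t distribution with noncentrality 1/SE, one-sided 0.025, on 2n − 2 degrees of freedom unadjusted and 2n − 3 adjusted.

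| Assumed r | Residual SD | Power, n = 40 per group | Power, n = 50 per group |
|---|---|---|---|
| 0 (unadjusted) | 1.60 | 78.8% | 87.2% |
| 0.2 | 1.57 | 80.4% | 88.5% |
| 0.3 | 1.53 | 82.5% | 90.0% |
| 0.4 | 1.47 | 85.3% | 92.2% |

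Example for r = 0.3, n = 40: residual SD = 1.6 × √0.91 = 1.526; SE = 1.526 × √(2/40) = 0.341; noncentrality = 1/0.341 = 2.93 on 77 degrees of freedom; power 82.5%.

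The 50-per-group column is an upper case, since it assumes that no information is lost to missing data. At r = 0 the only cost is one degree of freedom.

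**3. Chance imbalance.** A 1.96-SE imbalance in preoperative pain at 40 per group would shift the unadjusted NRS difference by 1.96 × √(2/40) × r × 1.6. That is 0.14, 0.21 and 0.28 points at r = 0.2, 0.3 and 0.4, against a margin of 1 point. Such imbalance averages to zero over randomisations, and the planned confidence interval already allows for it. In the one trial that is run, though, it could be neither seen nor adjusted for.

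**The case against.** The strongest objection is that this asks for an extra variable and shows no error. The pain co-primary is one postoperative score and not a change score. It needs no paired baseline, and the document promises no adjusted analysis. Randomisation makes the unadjusted comparison unbiased, and omitting a covariate does not raise the non-inferiority error rate. All of this stands.

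A reader might infer more from the text, in three ways that it does not support:
- *That the baseline section contradicts itself by claiming a baseline for both co-primaries.* The sentence concerns ultrasound and spirometry only, goes on to name diaphragmatic and pulmonary function, and is true of the primary endpoints through HDP. It needs no correction.
- *That missing NRS values have nothing to be imputed from.* Several baseline and intraoperative predictors are named, plus partial outcome data. Only baseline pain is absent.
- *That the sample size or the randomised comparison is unsound.* Neither depends on a preoperative score.

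It can also be said that the gain is small and rests on an assumed r. The PACU score follows a block of the operated region and intraoperative sufentanil, which may weaken any link with preoperative pain. This too stands: at r = 0 the gain is nil.

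Finally, Figure 1 is not shown and the article condenses a fuller protocol, so a preoperative score may be scheduled elsewhere. That is a reason to check first. It does not remove the point, because the Data collection section presents its list as the specific content to be collected, and a history of chronic pain cannot replace a score.

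**Conclusion.** The point holds as a modest, inexpensive improvement and not as an error. As the visible text stands, the NRS co-primary cannot be adjusted for, checked for balance on, or imputed from the patient's own earlier pain. The cost is precision: roughly 1.6 to 6.5 percentage points of power at 40 evaluable per group, and 1.3 to 5.0 at 50, for r between 0.2 and 0.4. These figures assume the protocol's SD of 1.6, a true difference of zero and an r that the document does not supply. The gain matters a little more because the planned size has no slack: at exactly 40 evaluable per group the planned t-test has 78.8% power, just under the 80% target. The conclusion also depends on Figure 1 and the full protocol not already including such a score.

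**What to change.** First confirm whether Figure 1 or the full protocol already schedules a preoperative pain score. If not:

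1. Add a resting shoulder NRS (0–10) to the blinded assessor's pre-block session, recorded before the allocation envelope is opened, and add it to the baseline list under Data collection and to the CRF.
2. Under Analysis of primary outcomes, estimate the NRS difference by ANCOVA with this score as covariate and the same 1-point margin. Alternatively, keep the t-test as primary and pre-specify the ANCOVA as supportive.
3. Add the score to the predictors under Handling of missing data.
4. Leave the purpose sentence in the baseline section as it is.

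The cost is one question at a session that already takes place, one CRF field, one degree of freedom and a line in the analysis plan. Patients enrolled before the change will lack the score, so a rule for the missing covariate is needed. Recruitment is scheduled from January to December 2026, so the sooner the question is added, the fewer such patients there will be.
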